## Abstract

Oral lichen planus is a chronic inflammatory disease of the oral mucosa characterised by immune dysregulation, but its pathogenesis remains incompletely understood and no curative treatment has been established. Our previous work showed that patients with oral lichen planus exhibit gut dysbiosis, including reduced microbial diversity and depletion of butyrate-producing bacteria. Because butyrate promotes regulatory T-cell differentiation and supports immune homeostasis, targeting this dysbiosis may represent a microbiota-directed approach for immune modulation in oral lichen planus. This study aims to investigate the effects of inulin supplementation on the gut microbiota and related immune markers in patients with oral lichen planus. This multicentre, double-blind, randomised, placebo-controlled parallel-group trial will enrol 80 patients with oral lichen planus. Participants will be randomly assigned in a 1:1 ratio to receive either inulin (8 g/day) or a maltose placebo for 4 weeks, in addition to standard care. The primary outcome is the change in the relative abundance of prespecified butyrate-producing gut bacteria from baseline to the end of intervention at Week 6. Secondary outcomes include changes in gut microbiota diversity, salivary microbiota composition, faecal short-chain fatty acid concentrations, peripheral blood regulatory T-cell counts, blood test parameters, and clinical symptoms of oral lichen planus. Analyses will follow the intention-to-treat principle, and between-group differences will be assessed using appropriate statistical methods. This trial is designed to evaluate, in a randomised placebo-controlled setting, whether a microbiota-directed intervention can modify gut microbial profiles and related immune markers in patients with oral lichen planus. The findings are expected to clarify whether inulin supplementation can modify gut microbial profiles and related immunological markers in patients with oral lichen planus. Trial registration: UMIN Clinical Trials Registry (UMIN-CTR), UMIN000060840, registered on 1 April 2026 (https://rctportal.mhlw.go.jp/detail/um?trial_id=UMIN000060840#).

## Introduction

Oral lichen planus (OLP) is a chronic inflammatory disease of the oral mucosa characterised by T-cell–mediated immune dysregulation [1,2]. Although OLP is relatively common in daily clinical practice, its aetiology and pathogenic mechanisms remain incompletely understood, and no curative treatment has been established [3]. Histopathologically, dense T-cell infiltration, including CD4⁺ and CD8^+^ T cells is observed in the lesional mucosa, suggesting that excessive immune activation contributes to the persistent inflammation.

In recent years, the gut microbiota has been recognised as a key regulator of systemic immune function [4]. Dysbiosis has been implicated in the development of various conditions, including allergic diseases, autoimmune disorders, and inflammatory bowel disease [5]. Our previous work demonstrated that patients with OLP exhibit reduced gut microbial diversity and a marked depletion of butyrate‑producing bacteria compared with healthy individuals [6]. Because butyrate‑producing bacteria promote the differentiation and function of regulatory T cells (Tregs) [7,8], their reduction may contribute to impaired immunoregulatory capacity and the chronicity of OLP.

Inulin is a soluble dietary fibre that acts as a prebiotic and promotes the growth of beneficial gut bacteria, particularly short‑chain fatty acid (SCFA) producers such as butyrate‑, acetate‑, and propionate‑producing taxa [9,10]. Randomised controlled trials in healthy adults have shown that inulin supplementation not only alters gut microbiota composition but also increases faecal SCFA concentrations [11]. Given that OLP is characterised by dysbiosis with reduced butyrate‑producing bacteria, inulin supplementation may help restore microbial balance and modulate immune responses.

However, no studies have investigated whether microbiota‑directed interventions can influence the disease biology of OLP. Therefore, this study aims to determine whether inulin supplementation increases the abundance of butyrate‑producing gut bacteria in patients with OLP. The findings of this trial are expected to provide foundational evidence for prebiotic supplementation as an adjunctive microbiota-directed strategy in OLP.

## Materials and methods

### Study design

This study aims to determine whether inulin, a prebiotic dietary fibre, increases the abundance of butyrate-producing gut bacteria in patients with oral lichen planus (OLP). It is a multicentre, double-blind, placebo-controlled, parallel-group randomised controlled trial. Eligible participants will be randomly assigned in a 1:1 ratio to receive either inulin (8 g/day) or a maltose placebo for 4 weeks, in addition to standard care. All participants will be followed for a total of 10 weeks, consisting of a 2-week pre‑observation period, a 4-week intervention period, and a 4-week post‑observation period. Baseline assessments will be performed at Week 2, immediately before the start of the 4-week intervention, and the primary endpoint will be assessed at Week 6, corresponding to the end of the intervention. Week 10 assessments will be performed as post-intervention follow-up.

### Study setting

The trial will be conducted at Kyushu University Hospital and the Department of Oral and Maxillofacial Surgery, Okayama University Hospital. Screening, randomisation, provision of study products, and follow‑up assessments will all be performed during routine outpatient visits.

### Trial organisation and oversight

Kyushu University serves as the coordinating site and is responsible for overall trial coordination and data management. Okayama University Hospital participates as a collaborating recruitment site and is responsible for study procedures conducted at that site. No steering committee, endpoint adjudication committee, or separate data monitoring committee has been established because this is a small, low-risk investigator-initiated trial of a dietary supplement.

### Eligibility criteria

#### Inclusion criteria.

Patients with oral lichen planus clinically diagnosed by a dentist and histopathologically confirmed.Men or women aged ≥18 yearsIndividuals who have received a full explanation of the study and have provided written informed consent of their own free will

#### Exclusion criteria.

Use of antibiotics within the past 3 monthsHospitalisation within the past 3 monthsRefusal to participate in the studyPregnant or possibly pregnant individualsKnown food allergy to inulin or plants of the Asteraceae familyAny other condition deemed inappropriate for participation by the principal investigator

### Recruitment and consent

Potential participants will be identified during routine outpatient care. Eligible individuals will receive written study information and an oral explanation from study staff, after which written informed consent will be obtained. Participation is voluntary, and participants may withdraw at any time without affecting their clinical care.

### Randomization

A stratified permuted block randomisation sequence will be generated before the start of enrolment by an independent allocation manager who is not involved in participant recruitment, treatment, or outcome assessment. Randomisation will be stratified by study site (Kyushu University Hospital and Okayama University Hospital) using variable block sizes to minimise the predictability of allocation. The allocation table for 80 participants will be generated using computer-based randomisation software and stored securely by the allocation manager.

After written informed consent is obtained and eligibility is confirmed, the enrolling investigator will contact the allocation manager to request the treatment assignment for the participant. The allocation manager will assign the participant to the next available allocation in the pre-generated sequence. At the time of each allocation, the allocation manager will record the registration date, date of consent, participant identification code, and the name of the enrolling investigator in a separate allocation log. The enrolling investigator will have no access to the allocation table or to future assignments, thereby ensuring adequate allocation concealment.

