### Sample size calculation

In our previous cross-sectional study, the mean relative abundance of butyrate-producing bacteria was approximately 12.4% (SD 8.1%) in patients with OLP and 14.7% (SD 8.2%) in healthy controls. Prior randomised trials in healthy adults have reported that inulin or inulin-type fructan supplementation at comparable doses can increase the relative abundance of fermentative taxa by approximately 5–15 percentage points, with concurrent increases in faecal short-chain fatty acid concentrations. On the basis of these data, we assumed that inulin supplementation would increase the summed relative abundance of the five prespecified butyrate-producing taxa by 12.5 percentage points from baseline, compared with 2.5 percentage points in the placebo group, yielding an expected between-group difference of 10 percentage points.

Because no prior intervention study has examined this response in patients with OLP, a conservative common standard deviation of 15% was adopted to account for expected variability in this patient population. Based on a two-sample comparison of the primary outcome between groups, assuming a two-sided significance level of 0.05, 80% power, and a standardised effect size of approximately 0.67, approximately 36 participants per group are required. Allowing for approximately 10% dropout, the target sample size was set at 40 participants per group, for a total of 80 participants. The calculation was performed using G*Power version 3.1.9.

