### Statistical analysis

All analyses will follow the intention-to-treat principle. Statistical tests will be two-sided with a significance level of 0.05 unless otherwise specified. Analyses will be performed using R (version 4.3.1 or later).

The primary outcome is the change from baseline to Week 6 in the combined relative abundance of five prespecified butyrate-producing taxa. The between-group difference will be assessed using a two-sample t-test or Mann–Whitney U test depending on distributional assumptions. ANCOVA adjusting for baseline values will be performed as a prespecified supplementary analysis. Because 16S rRNA gene sequencing data are compositional, a sensitivity analysis of the primary outcome using centred log-ratio transformation will be performed.

Secondary continuous outcomes will be analysed using ANCOVA models adjusting for baseline values. Repeated measures will be analysed using linear mixed-effects models with random intercepts to account for within-participant correlations and to evaluate time-by-group interactions.

Microbiome sequencing data will be processed using the QIIME 2 [13,14] platform. Taxonomic assignment will be performed using a prespecified reference database and classifier. Because species-level classification by 16S rRNA gene sequencing may be limited for some taxa, the primary analysis will use the most resolved taxonomic level that can be reliably assigned by the sequencing region and classifier. Taxa corresponding to the prespecified butyrate-producing bacteria will be aggregated according to a predefined taxonomic mapping before unblinding. Alpha diversity indices will be compared using parametric or non-parametric tests as appropriate. Beta diversity will be analysed using PERMANOVA based on UniFrac and Bray–Curtis distance matrices. Differential abundance analysis will be performed using LEfSe [15], with ANCOM-BC and/or ALDEx2 used as complementary approaches to account for the compositional nature of microbiome data. For multiple related comparisons, particularly microbiome taxa analyses, short-chain fatty acid comparisons, and immunological marker panels, false discovery rate correction using the Benjamini-Hochberg procedure will be applied. Adjusted p values will be reported alongside unadjusted p values where applicable.

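### Randomisation is stratified by site, but the primary test cannot include site and no model names it: the test is valid but slightly conservative

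*Protocol article*

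**What the plan says.** Allocation is 1:1 in permuted blocks, and site is the only stratification factor. Protocol article, Randomization: "Randomisation will be stratified by study site (Kyushu University Hospital and Okayama University Hospital) using variable block sizes".

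The Statistical analysis section then names the methods:

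- Primary outcome (change from baseline to Week 6): "The between-group difference will be assessed using a two-sample t-test", or a Mann–Whitney U test if the distribution calls for it.
- Support for the primary outcome: "ANCOVA adjusting for baseline values will be performed as a prespecified supplementary analysis".
- Secondary outcomes: "Secondary continuous outcomes will be analysed using ANCOVA models adjusting for baseline values".
- Repeated measures: "linear mixed-effects models with random intercepts to account for within-participant correlations and to evaluate time-by-group interactions".
- Beta diversity: "Beta diversity will be analysed using PERMANOVA based on UniFrac and Bray–Curtis distance matrices".

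Site, centre or stratum appears nowhere in that section. The sample size likewise rests on an unstratified two-sample comparison, "assuming a two-sided significance level of 0.05, 80% power, and a standardised effect size of approximately 0.67".

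**The concern.** Blocking within site balances the arms within each hospital, so a difference between hospitals in the outcome largely drops out of the treatment contrast. A pooled two-sample test does not take credit for this: it leaves the between-site variance in its standard error. The reported interval is then wider than the design warrants, and the test rejects a true null less often than 5%. Some efficiency that stratification made available goes unused.

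For the primary analysis, an unseen analysis plan does not settle the matter. The article fixes a test that has no place for a covariate, so site could enter only by departing from the stated method.

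**Working it through.** **Inputs from the Sample size calculation section.** Between-group difference 10 points (12.5 minus 2.5), SD 15, two-sided alpha 0.05, power 80%, 36 evaluable per group, about 10% dropout, 40 per group.

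**Inputs not in the documents, so assumed.** The share of outcome variance explained by site, R², from 0 to 0.20. The split of participants between sites, 50:50 or 70:30. Total SD is held at 15 throughout.

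**Step 1: the plan's own figure.** The normal approximation gives n = 2 × (1.96 + 0.84)² × (15/10)² ≈ 35.3, so 36 per group. The noncentral-t calculation gives power 0.8005 at 36 per group for an effect size of 0.67 (0.797 for 10/15). Then 36/0.9 = 40 per group and 80 in total. The stated figures reproduce.

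**Step 2: the standard error.** The unadjusted SE is 15 × √(2/36) = 3.54. Under site-stratified blocking the true SD of the estimate is about 3.54 × √(1 − R²). At R² = 0.10 that is 3.35. Simulation at R² = 0.10 gave a mean unadjusted SE of 3.53, an actual SD of 3.37, and a site-adjusted SE of 3.34 to 3.35.

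**Step 3: type I error and power (normal approximation).** With Φ the standard normal distribution function and 10/3.54 = 2.83:

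- Type I error, unadjusted: 2 × [1 − Φ(1.96/√(1 − R²))]
- Power, unadjusted: Φ((2.83 − 1.96)/√(1 − R²))
- Power, site-adjusted: Φ(2.83/√(1 − R²) − 1.96)

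**Step 4: simulation.** 10,000 trials per scenario, 72 participants, blocks of 4 or 6 within site, comparing the plain t-test with a linear model of treatment plus site. Monte Carlo standard error is about √(0.05 × 0.95/10,000) = 0.2 points for type I error and √(0.8 × 0.2/10,000) = 0.4 points for power.

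Results at 50:50 sites:

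| Assumed site R² | Type I error, unadjusted: formula / simulated | Power, unadjusted vs adjusted: formula | Power, unadjusted vs adjusted: simulated | Power forgone (points): formula / simulated |
|---|---|---|---|---|
| 0 | 5.0% / 5.0% | 80.7% vs 80.7% | 79.3% vs 79.2% | 0 / about 0 |
| 0.02 | 4.8% / 4.8% | 81.0% vs 81.5% | 79.8% vs 80.1% | 0.5 / 0.4 |
| 0.05 | 4.4% / 4.3% | 81.4% vs 82.7% | 81.4% vs 82.9% | 1.3 / 1.5 |
| 0.10 | 3.9% / 3.8% | 82.0% vs 84.6% | 81.1% vs 83.8% | 2.6 / 2.7 |
| 0.20 | 2.8% / 3.0% | 83.4% vs 88.5% | 82.0% vs 87.7% | 5.1 / 5.7 |

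With site in the model, simulated type I error stayed between 4.8% and 5.0%. Results at 70:30 were similar. The figures are for the t-test; the Mann–Whitney branch was not simulated.

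**Step 5: how large a site effect each R² implies.** With equal sites, the difference between sites in mean change must be 2 × 15 × √R² = 30√R²: 4.2 points at R² = 0.02, 6.7 at 0.05, 9.5 at 0.10 and 13.4 at 0.20. In the other direction, a 3-point difference gives R² = (3/30)² = 0.01.

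**The case against.** The strongest reply is that the effect is probably small. The primary outcome is a within-person change, so a stable difference in level between hospitals cancels; only a difference in four-week change counts. On the plan's own figures, R² = 0.10 needs about 9.5 points, close to the whole assumed treatment effect of 10. R² = 0.20 needs 13.4 points, more than the mean abundance of 12.4% reported for OLP patients. This stands, and it puts the primary outcome near the top rows of the table. It applies less clearly to PERMANOVA and the alpha-diversity comparisons, which are not described as change-based or baseline-adjusted.

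A second reply is that naming baseline as a covariate does not exclude others, and that full covariate lists are commonly left to the full protocol or analysis plan. For the secondary ANCOVAs, mixed models and PERMANOVA this largely stands: there the article is silent, not wrong. It does not answer the point about the primary test.

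A reader might infer that the sites process specimens separately, making large site effects likely. The documents do not say so. The Trial organisation section says only that Okayama is responsible for the procedures carried out there. Table 1 specifies central analysis and a standardised gating strategy for Tregs, and one QIIME 2 pipeline for gut and salivary sequencing.

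**Conclusion.** The mismatch between design and analysis is real, and for the primary outcome it is fixed by the choice of test. Its consequence is modest: a valid, slightly conservative test that forgoes some efficiency against a site-adjusted analysis. Over the assumed range of R² from 0 to 0.20 the forgone power runs from nil to 5–6 points. For the primary change score a loss of under 1 to about 1.5 points (R² up to 0.05) is the more likely part of that range. All of this depends on an R² that the documents do not give.

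A reader might infer that power falls below plan, that stratifying brings no benefit, or that false positives increase. None of these follows. Unadjusted power stays at about the planned 80% and rises somewhat as R² grows, because the estimate itself becomes more precise. Type I error falls below 5% and does not exceed it. The target of 80 is not wrong on this ground. This is a minor improvement to make, not a threat to validity.

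**What to change.** A site term cannot be added to a t-test or Mann–Whitney test, so the primary test has to change. Make the ANCOVA already planned as supplementary the primary analysis, with baseline value and site as covariates. If a rank test is needed, use a van Elteren test stratified by site. Name site as a fixed effect in the secondary ANCOVAs and mixed models, and as a term in PERMANOVA.

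The cost is 1 degree of freedom and an amendment that changes the primary test. No extra participants are needed, and if site has no effect power is essentially unchanged (79.3% vs 79.2% in simulation). The Ethical considerations section provides the amendment and registry route. The Trial status section reports that no outcome had been analysed at submission, so the change can be made before any outcome analysis.

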### Blinding

A blinding officer, independent of the allocation manager and enrolling investigators, will be responsible for ensuring the indistinguishability of the study products. The blinding officer will prepare a correspondence table linking sequential product serial numbers, the randomisation order, and product allocation codes (inulin or maltose). Based on this table, the blinding officer will label all study product sachets with their respective allocation codes only, so that neither participants nor investigators can identify the contents.

The correspondence table will be kept securely by the blinding officer and will not be disclosed to any other study personnel until unblinding. Unblinding will occur only in the event of a medical emergency requiring knowledge of the allocated treatment for appropriate clinical management of the individual participant. Full unblinding of all participants will be performed only after the database is locked and the analysis population and case eligibility decisions have been finalised.

Participants, enrolling investigators, outcome assessors, and data analysts will remain blinded throughout the study. During data analysis, group assignments will be coded (e.g., Group A and Group B) so that analysts remain unaware of which group received inulin and which received placebo. Unblinding of the data analysts will occur only after the primary analysis has been completed and the results have been locked.

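### The Blinding section claims analyst blinding for the whole study but lets it end at lock of the primary analysis, so secondary and sensitivity analyses may be run with arms known while a few choices are still open

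*Protocol article*

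**What the plan says.** The relevant statements are in two sections of the protocol article.

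**Blinding.** Four sentences bear on the analysts:
- The general claim: "Participants, enrolling investigators, outcome assessors, and data analysts will remain blinded throughout the study".
- The mechanism: "During data analysis, group assignments will be coded (e.g., Group A and Group B) so that analysts remain unaware" of which group received which product. It is not limited to the primary outcome.
- The milestone for the trial as a whole: "Full unblinding of all participants will be performed only after the database is locked and the analysis population and case eligibility decisions have been finalised".
- The milestone for the analysts: "Unblinding of the data analysts will occur only after the primary analysis has been completed and the results have been locked".

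**Statistical analysis.** Most secondary methods are named. For example, "Secondary continuous outcomes will be analysed using ANCOVA models adjusting for baseline values", and "Repeated measures will be analysed using linear mixed-effects models with random intercepts". PERMANOVA is named for beta diversity, LEfSe as the lead differential-abundance method, and Benjamini-Hochberg for multiplicity. Two items are left open: "Alpha diversity indices will be compared using parametric or non-parametric tests as appropriate", and LEfSe is to be supplemented "with ANCOM-BC and/or ALDEx2 used as complementary approaches". The same section makes the multiple-imputation sensitivity analysis of missing outcome data conditional on a judgement that missingness is at random.

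**The concern.** The general claim and the analysts' milestone do not describe the same period of blinding. Read together, they tell the reader that analysts are blinded for everything, and then that the protection can end once a single result is locked. The text does not say under which labels the remaining prespecified analyses are done.

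Coded groups exist so that a person making an analytic choice does not know which direction favours the intervention. If the codes are broken after the primary lock, any choice still open is made with both the primary result and the true arms known. The article treats this as a real risk elsewhere: it requires the taxonomic aggregation for the primary outcome to be settled before unblinding. The open choices in the secondary and sensitivity analyses do not get the same explicit protection.

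**Working it through.** No figure in the plan is in dispute, so the check sets the statements side by side.

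**Step 1: what the analysts' milestone requires.** The sentence names two conditions, completion of the primary analysis and lock of its results. It sets an earliest time. It neither says that other analyses follow unblinding nor requires them to precede it. Running them unblinded is therefore permitted, not scheduled.

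**Step 2: whether another sentence closes the gap.**
- The milestone for full unblinding depends on database lock and on final population and eligibility decisions. It protects the data and the analysis sets, not later choices of method.
- The coding sentence covers data analysis in general, which would include the secondary analyses. The next sentence then gives an end point tied to the primary analysis alone, so the coding sentence cannot be relied on beyond it.

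**Step 3: which choices are open once the primary analysis is locked.**

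| Analysis | Method in the article | Open after primary lock? |
|---|---|---|
| Primary outcome | t-test or Mann–Whitney, by distribution | No: chosen under codes |
| Taxonomic mapping for the primary outcome | Predefined, aggregated before unblinding | No |
| ANCOVA and centred log-ratio analyses of the primary outcome | Named | No |
| SCFAs, Treg counts, blood parameters, OLP-DAS | Covered by the named ANCOVA rule, with mixed models for repeated measures | No |
| Beta diversity | PERMANOVA | No |
| Lead differential-abundance method | LEfSe | No |
| Alpha diversity | Parametric or non-parametric | **Yes** |
| Complementary differential abundance | ANCOM-BC, ALDEx2 or both | **Yes** |
| Multiple imputation (sensitivity) | Run if missingness is judged to be at random | **Yes**, unless it counts as part of the primary analysis |

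The alpha-diversity entry has a further ambiguity. The indices are continuous secondary outcomes, so the general ANCOVA rule could also apply, and the article does not say which rule governs.

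**Step 4: whether timing forces an early reveal.** The Trial status section says that data cleaning and analysis begin only after data collection is complete. Week 10 data are therefore available when the primary analysis is run, and the secondary analyses need not wait for later data.

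**The case against.** The strongest reply has four parts.

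1. *The milestone is permissive.* This stands. A reader might infer that all secondary analyses will be run with the arms known. The documents do not say so, and the sponsor may intend to keep the codes throughout.

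2. *The secondary tests are mostly fixed.* This also stands. A reader might infer that the secondary outcomes as a group, including the immune and clinical ones, are exposed to a free choice of test. They are not: Treg counts and OLP-DAS fall under named models. Counting every secondary outcome as unprotected would treat fixed and open analyses alike.

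3. *The open details belong to the analysis plan or full protocol.* This stands in part. Neither document is shown, and either may settle the alpha-diversity test and the complementary method. It does not resolve the inconsistency, because the article itself states the blinding milestone. One could read the general claim as covering trial conduct only, which would remove the literal contradiction. It would still leave the secondary and sensitivity analyses without a stated blinding rule.

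4. *The harm is not an inflated error rate.* This stands. It is tempting to quote the type I error that results from picking the more favourable of two tests. That does not measure the effect of unblinding, because a two-sided p-value is unchanged when A and B are swapped. An analyst working under codes could pick in the same way. Unblinding adds knowledge of direction, and the documents give no basis for putting a number on that.

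**Conclusion.** The point holds as an inconsistency with a small practical consequence. The article claims analyst blinding for the whole study, yet the only stated end point is lock of the primary analysis. As written, secondary and sensitivity analyses may be run with true labels while three choices are open: the alpha-diversity test, the complementary abundance method, and the missing-at-random judgement.

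The effect is minor. The primary test is chosen and run under codes, outcome assessors are blinded, and full unblinding waits for database lock and final population decisions. The conclusion does not extend to the primary result or to the outcomes with named models.

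It rests on two assumptions: that the primary analysis in the milestone sentence means the primary test and not every analysis of the primary outcome, and that no document outside the article already extends the coding. If the first is wrong, the imputation judgement is protected and two open choices remain.

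**What to change.** Replace the analysts' milestone in the Blinding section with wording such as:

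> Data analysts will work with coded groups until the primary analysis, its supplementary and sensitivity analyses, and all prespecified secondary analyses (Weeks 6 and 10) have been completed and locked. Only exploratory and post hoc analyses will follow their unblinding.

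The general claim in the same section should then refer to this milestone, so that the two sentences agree.

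The coding already exists, and the labels are revealed only slightly later. The Trial status section reports that no outcome analyses had been performed at submission. If that is still so, the change can be made before any result is known. If the sponsor regards it as a substantial modification, the Ethical considerations section requires committee approval and a registry update.

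The change does not fix the open methods, and a marked primary result could still let an analyst guess the arms. It reduces the scope for choices driven by direction without removing it entirely.
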